## Abstract

**Introduction:**

Immune-inflammatory response plays a key role in the pathogenesis of atherosclerosis. IgG N-glycosylation is reported to be associated with the 10-year atherosclerotic cardiovascular disease risk score and subclinical atherosclerosis. However, the relationship of IgG glycosylation with actual clinical cardiovascular disease (CVD) events and plaque phenotypes has rarely been investigated. Therefore, this study aims to understand whether IgG glycosylation traits are correlated with actual clinical CVD events and plaque phenotypes.

**Methods and analysis:**

Designed to verify the efficacy of IgG glycosylation as a risk for CVD events and screen potential biomarkers of CVD to prevent atherosclerosis occurrence, this longitudinal prospective cohort study will be conducted at the First Affiliated Hospital of Shantou University Medical College, China. In total, 2720 participants routinely examined by carotid ultrasound will be divided into different groups according to plaque phenotype characteristics. Ultra-performance liquid chromatography will be performed to separate and detect IgG N-glycans in serum collected at baseline and at the end of the first, second and third years. The primary outcome is the actual clinical CVD composite events, including non-fatal myocardial infarction, death due to coronary heart disease, and fatal or non-fatal stroke.

**Ethics and dissemination:**

The Clinical Ethics Committee of the First Affiliated Hospital of Shantou University Medical College approved this study (number: B-2021-127). Findings of this study will be submitted for publication in peer-reviewed journals.

**Trial registration number:**

ChiCTR2100048740.

Strengths and limitations of this studyThis study is a longitudinal prospective cohort study which will indicate change in IgG glycans in people 50–65 years of age.The feasibility of this study is high as it does not require treatment of participants with drugs or surgery.Due to the protective effects of oestrogen on atherosclerosis, this study will only involve postmenopausal women.The cohort is derived from a single centre and represents only one ethnic group, Han Chinese, which will lack ethnic diversity, and the results might not be applicable to the general population.Some biases, such as loss to follow-up and other uncontrollable factors, may exist, although this study is designed to control the biases.

## Introduction

### Background and scope

Atherosclerosis (AS) is a cardiovascular disease (CVD) with high morbidity and mortality, accounting for approximately 20% of all deaths worldwide.^1^ Ischaemic heart disease (IHD), ischaemic stroke and peripheral vascular disease are the main serious outcomes caused by AS.^2^ However, the pathogenesis of AS remains obscure. The main risk factors for AS are family history, hypertension, smoking, dyslipidaemia, diabetes and obesity. Other factors such as metabolism disorders, platelet activation, thrombosis, intimal damage, inflammatory response, oxidative stress and vascular smooth muscle cell activation jointly promote the occurrence and progression of AS.^3–5^ In addition, whether some novel factors, such as suboptimal health status and telomere length in peripheral blood leucocytes, could increase the risk of atherosclerotic cardiovascular disease (ASCVD) is being investigated.^6–8^

Studies show that immune inflammation exerts a significant role in atherogenesis.^9^ Animal experiments indicate that the initiation, growth, differentiation and rupture of atherosclerotic plaques are influenced by the immune system.^10^ A randomised controlled trial involving 10 061 patients demonstrated that targeted immune anti-inflammatory pathway therapy significantly reduces CVD events, independent of lowering lipid levels.^11^ Furthermore, germinal centre-derived IgG is a determinant of plaque size and stability and effectively maintains the molecular properties of the aorta.^12^ Therefore, the interaction of the adaptive immune system modulates the progression of AS.

Glycosylation is the most abundant and diverse form of post-transcriptional modification in organisms, involved in almost every physiological process, including immune responses.^13 14^ Alterations in protein glycosylation are considered as the major event in the transition from health to disease status.^14^ It has been demonstrated that IgG glycans are associated with a variety of diseases, such as immune system diseases,^15^ cancers,^16–18^ nervous system disease, 19 infectious diseases^20 21^ and haematological system diseases.^22^ Driven by specific enzymes, the complex carbohydrates attached to immunoglobulins have specific regulatory effects, which lead to differences in immune function.^23^ A study revealed that glycosylation changes, especially for the most abundant IgG in circulation, directly affect its inflammatory properties.^24^ For example, the anti-inflammatory and proinflammatory activity of IgG are determined by sialylation and agalactosylation, respectively.^25 26^ Furthermore, a cross-sectional study indicated that deficiency in galactose and sialic acid correlates with blood lipid levels.^27^ As the major elements of life, the communication between glycans and lipids even be proposed as a paracentral dogma.^28^ Therefore, considering the significant role of inflammation, especially immune inflammation in CVD development, different IgG glycosylation traits may stratify the risk phenotypes for CVD development.

Phenotypes of plaque include with or without plaque, plaque stability, size, location and number. A cross-sectional study based on two independent cohorts reported that the glycosylation traits of IgG are associated with the 10-year ASCVD risk score, subclinical AS and risk factors for CVD, such as smoking, high-density lipoprotein cholesterol and type 2 diabetes mellitus.^29^ However, it is unclear whether IgG glycosylation correlates with actual clinical CVD events and plaque phenotypes. Thus, we hypothesise that IgG N-glycan profiling is an independent prognostic indicator of actual clinical CVD composite events.

### Objectives

We aim to understand whether IgG glycosylation traits are correlated with plaque phenotypes and actual clinical CVD composite events, including non-fatal myocardial infarction, coronary heart disease death, and fatal or non-fatal stroke.

## Methods and analysis

### Design and setting

This study is an observational, single-centre longitudinal prospective cohort study to be conducted at the First Affiliated Hospital of Shantou University Medical College (SUMC), Guangdong, China. The protocol applies the checklists of the Standard Protocol Items: Recommendations for Interventional Trials (SPIRIT) 2013 statement,^30^ a guideline for clinical trial design.

### Participants

This study will be conducted in the Health Care Centre of the First Affiliated Hospital of SUMC, where people over 50 years old are routinely recommended to be examined by carotid ultrasonography for early diagnosis and detection of carotid atherosclerosis (CAS) and early prevention of CVD events. After the clinical study was registered on 15 July 2021, participants conventionally undergoing carotid artery ultrasound examination will be recruited and divided into different groups according to carotid plaque phenotypes (figure 1). Potential eligible participants will be recorded in real time by a sonographer. The research team consists of physicians familiar with ultrasound examination and academic staff skilled in clinical study design and statistical analysis. Furthermore, all investigators will obtain the required research-related training before the start of the study.

**Figure 1 F1:**
[figure not shown]
Participant distribution in the study. CAS, carotid atherosclerosis; CVD, cardiovascular disease; UPLC, ultrahigh-pressure liquid chromatography.

### Inclusion criteria

Prospective participants will be carefully evaluated based on the following inclusion criteria:

Age between 50 and 65 years old.Had carotid ultrasound performed.Participants or their families provided informed consent.

### Exclusion criteria

Participants with any of the following will not be enrolled in the study:

Participants with complications such as IHD, stroke, infection, immune system disease, nervous system disease, haematological system disease and cancer.History of lipid-lowering therapy.History of anticoagulant therapy or antiplatelet therapy or vasodilator therapy.History of intravenous immunoglobulin or blood transfusion within 1 month.Irregular follow-up.

### Withdrawal

Participants may withdraw their participation from the study for any reason.Other circumstances: based on the investigator’s judgement, the participant no longer meets the study criteria for any reason.

### Blinding

Participants, sonographers, data gatherers and data analysts are not blinded to group assignments, whereas specimen examiners and follow-up staffers are blinded.

### Data collection and management

Information from the enrolled participants, including smoking history, diabetes status and antihypertensive medication, along with low-density lipoprotein (LDL), high-density lipoprotein, triacylglycerol and total cholesterol levels, will be assembled. In addition, a sonographer will inspect the characteristics of carotid plaque, including plaque size, number, site, blood flow, echo, shape and stability. All data will be kept through EpiData (V.3.1; Denmark), an electronic data capture applied for data entry. Furthermore, 1 mL serum will be collected from each participant at different times (enrolment, first year, second year and third year) after being centrifuged at 604 *g* for 10 min at 277.15 K. Serum will be stored in the freezer at −80℃ for biochemistry and glycan analysis.

### Follow-up

The survival status (surviving/deceased) and actual clinical CVD composite events of the participants, including CVD death, myocardial infarction and stroke, will be followed up at the end of the first, second and third years by two trained investigators through telephone, outpatient visit and physical examination. Furthermore, serum samples will be collected every year and used for detection of IgG glycans (figure 2).

**Figure 2 F2:**
[figure not shown]
Schedule of enrolment, distribution and assessment in the study. CAS, carotid atherosclerosis; CHD, coronary heart disease; D, day; HDL, high-density lipoprotein; LDL, low-density lipoprotein; MI, myocardial infarction; TC, total cholesterol; TG, triacylglycerol; UPLC, ultrahigh-pressure liquid chromatography; W, week; Y, year.

### Sample size

It has been reported that the incidence of CVD events is about 6%.^31^ According to Liu *et al*,^32^ among 24 IgG glycan peaks (GPs), GP6 is significantly different between people with and without ischaemic stroke (5.00 (4.26, 5.85) vs 4.48 (3.93, 4.35), p=0.028) and therefore can be used to roughly estimate the sample size. Converting median and quartile to mean and SD is necessary for the sample size.^33–35^ Taking the incidence of CVD events and this conversion into consideration, 2267 participants will be needed, based on an α of 0.05 on a two-sided test and 90% power, to obtain a statistical difference. An additional one-fifth is required for the total sample size when considering cases of lost to follow-up and refusal to visit. Finally, a total of 2720 participants are required for the study. The sample size was calculated using PASS software (V.11; NCSS, America).

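### The sample size rests on an impossible GP6 quartile and a 6% incidence with no time period, so the stated 90% power cannot be verified at 2267

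*Protocol article*

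**What the plan says.** The Sample size section of the protocol article uses two inputs. The first is a GP6 comparison from a cited study of people with and without ischaemic stroke: "5.00 (4.26, 5.85) vs 4.48 (3.93, 4.35), p=0.028". The section treats these as medians with quartiles and says "Converting median and quartile to mean and SD is necessary for the sample size". The second is an event rate: "It has been reported that the incidence of CVD events is about 6" per cent, with no period attached.

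From these it concludes that "2267 participants will be needed, based on an α of 0.05 on a two-sided test and 90% power", adds one-fifth for loss and refusal, and arrives at 2720. It does not say how the 6% entered the calculation beyond "Taking the incidence of CVD events and this conversion into consideration".

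Elsewhere, the Follow-up section sets yearly contacts to the end of year three, and the Inclusion criteria limit age to 50 to 65. The Exclusion criteria remove "Participants with complications such as IHD, stroke, infection, immune system disease" and others, including anyone with a history of lipid-lowering, anticoagulant, antiplatelet or vasodilator therapy.

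**The concern.** An upper quartile cannot be smaller than the median of the same sample, so the second group's printed summary cannot be right, and neither can any mean and SD converted from it. This comparison is the only effect size behind the only power statement in the article.

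The other input, 6%, sets the number of events, and events drive the power of a comparison this unbalanced. At 2267 evaluable participants, 6% means 136 events, 3% means 68 and 2% means 45. Whether 6% is a 3-year risk, and whether it suits a population without IHD, stroke or lipid-lowering or antiplatelet treatment, cannot be told from the text. A reader therefore cannot tell which effect the cohort has 90% power to detect.

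**Working it through.** **Inputs from the Sample size section.** Two-sided α 0.05 and 90% power, so (1.960 + 1.2816)² = 10.507; the GP6 medians and quartiles; 6% incidence; 2267. The conversion, test and allocation are not printed. I assume mean = (Q1 + median + Q3)/3 and SD = (Q3 − Q1)/1.35, and also try the median used as the mean.

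**1. Can 2267 be reproduced from the printed values?**

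- With stroke: mean (4.26 + 5.00 + 5.85)/3 = 5.037; SD 1.59/1.35 = 1.178.
- Without stroke: mean (3.93 + 4.48 + 4.35)/3 = 4.253; SD 0.42/1.35 = 0.311.
- Difference 0.783.

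For a 6:94 split, N = 10.507 × (s₁²/0.06 + s₂²/0.94)/difference²:

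| Variance used | Converted means (difference 0.783) | Medians as means (difference 0.52) |
|---|---|---|
| Unequal | 398 | 902 |
| Average of the two | 225 | 511 |
| First group's SD in both | 421 | 956 |

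If a 1:1 group size is divided by 0.06 instead, converted means give 25.4/0.06 = 424 (450 with a Mann-Whitney adjustment and rounding up), and medians as means give 57.7/0.06 = 961. A wider set of conversions, variance choices and tests runs from 51 to 1050. None comes near 2267.

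Power at 2267 with the printed values: SE = √(1.178²/136 + 0.311²/2131) = 0.101. Then 0.783/0.101 is about 7.7, or 0.52/0.101 about 5.1 with medians as means. Both give power above 99.9%.

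**2. Would a one-digit misprint explain it?** Suppose the quartile is 5.35 (assumption).

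- Mean (3.93 + 4.48 + 5.35)/3 = 4.587; SD 1.42/1.35 = 1.052; difference 0.450; effect 0.403 SD.
- 1:1 group size: 10.507 × (1.178² + 1.052²)/0.450² = 129.4.
- Mann-Whitney adjustment: 129.4 × π/3 = 135.5, rounded up to 136.
- 136/0.06 = 2266.7, so 2267.

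This matches exactly. But the 136 is a size for two equal groups, and the cohort would have 136 events against 2131 non-events. There SE = √(1.178²/136 + 1.052²/2131) = 0.1035, and 0.450/0.1035 − 1.96 = 2.39, which is about 99% power. With the same inputs, direct 6:94 sizing with unequal variances needs about 1261.

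**3. What if 2267 was sized directly at 6:94?** The detectable effect would be 3.2416 × √(1/136 + 1/2131) = 0.287 SD, which the article does not print.

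**4. Power at 2267 evaluable, by 3-year incidence (normal approximation):**

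| 3-year incidence | Events | Quartile 5.35 (0.403 SD) | Direct 6:94 sizing (0.287 SD) |
|---|---|---|---|
| 6% | 136 | 99% | 90% |
| 4% | 91 | 95% | 76% |
| 3% | 68 | 88% | 64% |
| 2% | 45 | 72% | 48% |
| 1.8% | 41–42 | 68% | 44–45% |

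The last row applies if 6% were a 10-year figure at a constant rate (assumption): 1 − 0.94^0.3 = 1.84%. For the 5.35 column, a Welch calculation gives 99%, 87%, 70% and 66% at 6%, 3%, 2% and 1.8%.

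**5. Loss allowance.** 2267 × 1.2 = 2720.4, which agrees with 2720. This step is not in question.

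**The case against.** The best reply is that this is a typing error in an article, not a faulty calculation. Changing one digit restores 2267 exactly. The conversion methods are cited, and an article may leave the formula, the converted means and the test to the full protocol. The section also calls its estimate a rough one. Most of this stands: a misprint is plausible, and the unprinted conversion is not itself a fault. It does not settle the matter, because the match needs an altered digit, an unstated Mann-Whitney adjustment and an unstated 1:1 step. Even then the cohort's power at 6% is about 99%, not 90%. It also leaves the incidence without a period.

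Three stronger readings are tempting but unsupported.

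- *The study is underpowered.* The lowest figures combine 0.287 SD with a low incidence, and the article states neither. If 6% is the 3-year risk, power is at least 90% in both columns of the table. With the printed digits taken literally and the converted means, it is about 99% even at 1.8%.
- *The true quartile must be near 5.65.* That follows only from direct 6:94 sizing, which the article does not describe; 5.35 also leads to 2267.
- *A null result could not be interpreted.* Interpretation would rest on the observed events and confidence intervals, not on the planning paragraph.

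**Conclusion.** The point holds in this form. One printed input is impossible, 2267 does not follow from the inputs as printed, and the incidence lacks a time period that can be matched to three years of follow-up. These three facts need no assumption beyond the usual conversions.

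The consequence is that 90% power cannot be verified. At 6% the printed values imply over 99.9%, the assumed 5.35 about 99%, and direct 6:94 sizing 90% by construction. The incidence matters more than the digit. Between 6% and 2% over three years, power falls from about 99% to 72% under the first assumption and from 90% to 48% under the second. The documents do not say which effect size or which incidence applies, so they show neither adequate nor inadequate power.

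**What to change.** Rewrite the Sample size paragraph and leave the total at 2720:

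- Check the second group's upper quartile against its source and correct it.
- State the effect size that the calculation used, and whether it was sized at 1:1 and divided by 0.06 or directly at 6:94.
- Give the period to which the 6% refers, and the incidence expected over three years under these age limits and exclusions.
- Restate the cohort's power, or its detectable effect, over a range of 3-year incidences such as 2% to 6%. Take the effect size from the corrected source, not from the back-calculated values above.

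The cost is one paragraph and no extra participants. The stated power may become less favourable.

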### Carotid ultrasound

Colour Doppler ultrasonography (Siemens Acuson X150) will be used to scan the carotid artery. Participants will be held on a supine position with the head turned to the opposite side and the probe moved from the root of the neck to the head. The common carotid artery, bifurcation, internal carotid artery and external carotid artery are scanned. Based on the diameter, plaque morphology and echo characteristics, the plaques are classified into three types (soft plaques: uniform or uneven images, irregular form, weak and low echo; hard plaques: strong echo, uneven thickening of the tube wall with enhanced echo and sound shadow behind; mixed plaques: uneven echo, unequal intensity, irregular shape, large image range). Hard plaques are defined as stable plaques, while soft and mixed plaques are regarded as unstable plaques.

### Ultrahigh-pressure liquid chromatography

IgG glycosylation will be detected by ultrahigh-pressure liquid chromatography (UPLC) (LC-30AD, Shimadzu). First, IgG will be isolated with a protein G extraction plate. After being dried and exposed to peptide-N-glycosidase F, N-glycan will be released and labelled with 2-aminobenzamide fluorescent dye. Furthermore, the free markers and reducing agents will be removed by hydrophilic chromatography-solid phase extraction. Subsequently, fluorescently-labelled N-glycans will be separated by hydrophilic chromatography on UPLC.^36^ Finally, an automatic processing method with a traditional integration algorithm is used for data processing. Each chromatogram is manually corrected to ensure the same integration interval for all samples.

### Outcome measurements

The primary outcome of this study is the composite events of CVD. The secondary outcome is the 3-year mortality by counting all-cause death.

### Statistical and analytical plans

Categorical variables will be expressed by frequency (percentage) and univariate analysis will be performed using the χ^2^ test. Data of normal distribution are shown as mean±SD. The t-test and analysis of variance are used for comparison of two groups and multiple groups, respectively. Non-normally distributed data are represented by median (P25, P75). Univariate analysis is performed by non-parametric testing. Interpolation is carried out according to the type of data loss. If the lost data are of numerical type, the average value is used to fill it. However, if the lost data are non-numerical, the value with the highest occurrence frequency in this index is filled in. Logistic regression will be applied to analyse the association between IgG N-glycosylation characteristics and CVD events. Subsequently, a glycan risk score will be created to evaluate the associative effects of all glycan traits screened. A p value <0.05 indicates statistical significance. SPSS software (V.26.0) will be used for statistical analysis.

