Glycoprotein acetylation (GlycA), a more reliable compound biological marker of systemic inflammation, has potential value in predicting CVD outcomes and reflecting inflammation.^29 44–47^ However, GlycA is a glycan signal of a single measure based on nuclear magnetic resonance. Therefore, the association between IgG N-glycosylation with richer glycoprotein traits and CVD composite events will be assessed in this study. If the results of this study show a significant correlation between IgG glycosylated traits and actual clinical CVD composite events, it will provide further evidence on the role of glycosylation modification and immune-inflammatory response in AS, as well as a potential biomarker better than GlycA in predicting CVD events in the clinic. In addition, clarifying the correlation between IgG and AS and revealing the mechanism of atherogenesis are essential to providing new directions for treatment and prevention of CVD. Our study will provide important scientific significance and socioeconomic value for improving the quality of life and decreasing the mortality rate and the socioeconomic burden of patients with CVD.

However, some limitations to this study exist. First, the participants are recruited at a single centre and represent only one ethnic group, Han Chinese, in the Chaoshan area of Guangdong Province and thus lack ethnic diversity. Further, a multicentre cohort study is required for application of results to the general population. Second, follow-up bias is inevitable in this prospective cohort study due to the existence of subjects who may migrate, leave or withdraw from this cohort, although the authors will try their best to control it.

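### Logistic regression on event status, with lost status open to filling as 'no event' and no rule that the glycan sample precedes the event, is a weak test of prognosis

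*Protocol article*

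**What the plan says.** The hypothesis (Background and scope) is that "IgG N-glycan profiling is an independent prognostic indicator of actual clinical CVD composite events". The composite is described in the abstract as "including non-fatal myocardial infarction, death due to coronary heart disease, and fatal or non-fatal stroke", so some people with an event survive it and can be sampled again.

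Participants "will be followed up at the end of the first, second and third years by two trained investigators" (Follow-up). In the same section, "serum samples will be collected every year and used for detection of IgG glycans"; Data collection and management lists four samples per person, at enrolment and at years one, two and three.

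The model, in Statistical and analytical plans, is: "Logistic regression will be applied to analyse the association between IgG N-glycosylation characteristics and CVD events". That section does not say which sample supplies the glycan value. It fills missing numerical data with the mean and missing non-numerical data with the most frequent category, and makes no exception for the outcome.

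Losses are expected. Sample size adds one-fifth to 2267 participants to reach 2720, and the Discussion says that "follow-up bias is inevitable in this prospective cohort study due to the existence of subjects who may migrate, leave or withdraw". The strengths list describes a "longitudinal prospective cohort study which will indicate change in IgG glycans in people 50–65 years of age", but the tests named compare groups and none is specified for repeated values within a person.

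**The concern.** Two features of the stated analysis sit badly with a prognostic aim.

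First, a binary outcome model has no place for partial follow-up. Someone last seen at year one must be dropped, coded event-free, or have a status filled in. The stated filling rule, applied to event status, gives 'no event' every time, because about 94% of people have none. If people with high (or low) glycan values leave more often, their unseen events become non-events selectively and the association is distorted.

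Second, glycans are assayed in the same years in which events occur. If a sample drawn after a myocardial infarction or stroke serves as the exposure, a change caused by the event is read as a predictor of it. The study could then report a prognostic marker that is only a consequence of disease.

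**Working it through.** **Inputs.** From Sample size: 2267 needed, 2720 recruited, event incidence about 6%. The inflation reproduces: 2267 × 1.2 = 2720.4. The implied loss is (2720 − 2267)/2720 = 453/2720 = 0.167, or one-sixth. The 2267 itself could not be reproduced from the printed GP6 quartiles (one median, 4.48, lies above its own upper quartile, 4.35). That is a separate matter, and nothing below depends on it being right.

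Assumptions: the 6% is a three-year risk (the article gives no period), and the whole one-fifth allowance is loss to follow-up. Expected events are then 0.06 × 2720 = 163 among all recruited, or 0.06 × 2267 = 136 among 2267.

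**Losses coded event-free.**
- If people leave evenly over three years, a lost person is unobserved for half the period on average. Events missed: 1/6 × 1/2 = 1/12 = 8.3%, or about 14 of 163.
- Upper bound, every lost person filled as 'no event': 163/6 = 27 events recoded, and the observed risk falls from 6.0% to (163 − 27)/2720 = 5.0%.
- Dropping them instead discards 453 people with 1.5 years of valid follow-up each on average.

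**Does this bias the association?** Simulation: N = 2720, 6% three-year risk, about one-sixth lost, baseline glycan as exposure, lost people coded event-free in the logistic model and censored in the Cox model, 400 runs per setting. 'Related loss' means a log hazard of loss of 0.5 per SD of glycan (assumption).

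| Loss | True log HR per SD | Logistic: rejects (mean coefficient) | Cox: rejects (mean coefficient) |
|---|---|---|---|
| Random | 0.28 | 92.8% (0.293) | 93.0% (0.284) |
| Related | 0 | 11.8% (−0.059) | 6.2% (−0.009) |
| Related | 0.28 | 72.8% (0.227) | 89.8% (0.275) |

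The simulation error on 11.8% is √(0.118 × 0.882/400) = 1.6 percentage points, so the excess over 5% is not noise.

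**Post-event sera.** Take 136 cases and 2267 − 136 = 2131 non-cases, and a glycan with no prognostic value. Assume 60% of cases (82) contribute a post-event sample shifted by δ SD and the other 54 contribute an unshifted one. The mean shift is δ × 82/136 = 0.603δ. The standard error is √(1/136 + 1/2131) = 0.0884. The false-positive rate is about Φ(0.603δ/0.0884 − 1.960).
- δ = 0.2: 1.364 − 1.960 = −0.596, giving 28%.
- δ = 0.3: 2.045 − 1.960 = 0.085, giving 53%.

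If all 136 cases were shifted, the rates would be 62% and 92%. Neither the shift nor the 60% comes from the article.

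**Sample size under a Cox model.** With 136 events, the log hazard ratio detectable with 90% power is (1.960 + 1.282)/√136 = 0.278 per SD, a hazard ratio of 1.32. The matching case/non-case comparison needs a standardised difference of 0.287, so the sample size need not change.

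**The case against.** Much can be said for the plan. Follow-up is a fixed three years, status is checked annually and risk is low. In that setting logistic regression on a baseline exposure performs almost as well as Cox when loss is random (92.8% against 93.0%). A reader might infer that ignoring event times is itself a serious loss; the figures do not support that.

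A reader might also infer material bias from competing deaths. Counting a non-CVD death as no CVD event is correct if the target is crude three-year risk. The article gives no non-CVD death rate, and at ages 50 to 65 over three years the effect is probably minor.

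On sampling, the article never says that follow-up sera enter the logistic model, and a prognostic hypothesis points towards baseline values. Ischaemic heart disease and stroke are exclusion criteria, and the Withdrawal section lets the investigator remove someone who no longer meets the criteria, so survivors of an event might leave sampling. The text does not settle this. It supports only that post-event sera can enter, not that they will.

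Finally, an article may leave detail to an analysis plan. That covers part of the exposure question and the model for change. It does not cover the outcome model and the filling rule, which the article states.

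**Conclusion.** The point holds in two parts. The firmer part is that the stated combination of a binary model and most-frequent-value filling suits a cohort with expected losses poorly. On the assumptions of a 6% three-year risk and one-sixth lost, it misses about 8% of events if people leave evenly and recodes at most about 27 of 163. Whether that biases the association depends on loss being related to the glycan, for which the article gives no figure.

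The second part is that the exposure sample is not fixed, so reverse causation is not ruled out. The 28% to 53% range illustrates its possible size and rests wholly on assumed inputs. A reader might compare only the 82 shifted cases with the non-cases and obtain 43% and 76%; that leaves out the other 54 cases and should not be used.

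This should be changed because a better-suited analysis is available at little cost. It does not show that logistic regression is invalid here.

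**What to change.** Rewrite the association paragraph in Statistical and analytical plans so that:

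- The primary analysis is a Cox model (or a discrete-time complementary log-log model for annual intervals) of time to first composite event on the baseline glycan value. Follow-up is censored at last contact and, for the cause-specific hazard, at non-CVD death.
- Missing event status is never filled; the filling rule expressly excludes the outcome.
- Year 1 to 3 glycan values enter event models only as time-dependent covariates measured before the event, as a secondary analysis. Post-event samples are excluded.
- Change in glycans is described with a linear mixed model.

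Cost: mainly wording, and SPSS fits Cox and mixed models. There is also a data requirement: the event date, or at least the annual interval in which the event fell, and the last-contact date must be recorded for everyone. The Follow-up section mentions annual status but no dates, so the record form should be checked while follow-up can still supply them. The sample size is unaffected. Cox regression does not remove bias if loss depends on event risk in ways the model's covariates do not capture, so reasons for loss should be recorded too.
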